#### Statistics

The primary end point of disease progression (10% relative FVC decline or death within 12 months) will be used dichotomously across all subgroups collectively analysed together, with the exception of IPF controls. Association of baseline biomarker levels with dichotomous disease progression and overall survival will be analysed using binomial family of generalised linear models, while Gaussian family or otherwise appropriate models will be used to assess associations with continuous secondary end points. The Benjamini-Hochberg procedure will be applied to account for multiplicity as appropriate. Repeated measures mixed models will be used to assess associations over time, which includes time points within one model and circumvents correction for multiple testing. Fixed factors will include baseline demographic information. Where putative biomarkers are identified, end point data will be used to compare biomarker levels by time-to-event through proportional hazard models; comparable ability to predict end points will be assessed through sensitivity and specificity analyses (receiver operator characteristic curves).

To identify transcriptomic biomarkers, RNA-seq libraries will be prepared and entered into a workflow for read count normalisation enabling quantification of transcript expression; normalisation ensures length and abundance of cDNA reads are corrected according to other genes (reads per kilobase per million) and further library scaling can occur.^25 26^ Libraries, aligned to an appropriate reference genome, will enable detection of differential gene expression and SNPs/variants according to primary end point and secondary measures of disease severity. Transcript-discovery artefacts, transcripts that remain below detectable levels of change across compared samples, as well as any with zero mapped reads will be excluded. R statistical packages will be used for these bioinformatics workflows.

Further statistical analyses will be performed to determine associations between identified biomarkers and exploratory secondary objectives. Statistical approaches include, but are not limited to, correlation and analyses of variance between biomarker levels and patient-reported QoL outcomes or disease exacerbations; machine learning strategies on home spirometry to detect decline in lung function, and subsequent comparison of sensitivity with traditional spirometry measures at predicting end points. Factor analysis approaches will be used to reduce dimensions of data sets and assess clustering; generalised linear models will be used to test associations.

Confounding factors are particularly important in studies that hope to offer causal inference of biomarkers on clinical outcomes,^27^ and corrections to adjust for these will be applied in the analysis as proposed by the directed acyclic graph (figure 2).^28^ Fixed factors in mixed models will include baseline demographic information: age, gender, body mass index and smoking status. Exposure history in patients with chronic HP will be collected as will time from diagnosis to enrolment across all subgroups and adjusted for as a potential confounder. Some participants may be on background therapies such as immunosuppression and corticosteroids. While these therapies are likely to be confounders, it is possible they may decrease or increase progression of fibrosis based on the PANTHER (Prednisone, Azathioprine, and *N*-Acetylcysteine: A Study That Evaluates Response in Idiopathic Pulmonary Fibrosis) Study.^29^ Therefore, models will include treatment strategy as part of the minimal set of adjustment for estimating direct effect on end point. The objectives of the study do not extend to assessing treatment effect. Further unknown confounders will be identified from the spirometry smartphone application that will collect various data such as air quality index to inform limitations and future study.

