## Methods and analysis

### Objectives

INJUSTIS is a prospective multicentre observational cohort study that will be managed through the Nottingham Respiratory Research Unit and funded by the National Institute of Health Research (NIHR) through the Nottingham Biomedical Research Centre and an NIHR professorship ([name]).

The primary objective is to:

Identify biomarkers that determine progressive fibrotic lung disease irrespective of aetiology.

The secondary objectives are to:

Identify biomarkers that predict all-cause mortality.Identify biomarkers that predict changes in QoL scores.Identify biomarkers that predict the development of disease complications (respiratory failure and acute exacerbations).Investigate genetic association and epigenetic modifications which affect fibrotic disease severity and progression.Prospectively evaluate longitudinal disease behaviour in patients with non-IPF fibrotic lung diseases with a view to developing composite clinical end points for subsequent use in intervention studies.Explore association of environmental exposures with disease progression and all-cause mortality.Investigate whether home handheld spirometry over 3 months predicts disease progression and survival.

The primary end point will be:

Disease progression defined as relative forced vital capacity decline ≥10% or death within 12 months.

Secondary end points are:

All-cause mortality at time of censoring.Number of acute exacerbations over 2 years.Change in Quality of Life (QoL) Questionnaire Scores from baseline to 12 weeks.Rate of change in biomarker activity from baseline to 12 weeks.Change in diffusing capacity of the lung for carbon monoxide (DLco) from baseline to 12 months.Change in 6 min walk distance from baseline to 12 months.Change in transcriptomic profiles from baseline to 12 weeks.Change in home handheld spirometry values from baseline to 12 weeks.

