#### Study regimen

Both cases and IPF controls will undertake the same investigations. Following informed consent, the following test results, previously carried out as part of the participant’s usual NHS care, will be used for the purposes of the study:

HRCT findings.Blood results.Lung function tests.Bronchoscopy samples if already taken.

All participants will have baseline investigations at the first visit having provided informed consent. At the first visit, 40 mL of blood will be obtained, full lung function tests and a 6 min walk test will be performed. Participants will also be asked to complete QoL Questionnaires (Medical Research Council Dyspnoea Scale,^20^ Leicester Cough Questionnaire,^21^ IPF-abridged Profile for Assessment and Referral to Care,^22^ King’s Brief ILD Questionnaire^23^ and EQ-5D-5L).^24^ If consent is given for optional bronchoscopy, this will be subsequently performed and bronchoalveolar lavage carried out. Participants with a smartphone will be given the option of a home handheld spirometer and asked to provide daily FVC readings for the first 3 months of the study period.

Further visits at 3 months, 12 months and 24 months will include further 40 mL blood sampling, QoL and full lung function analysis. At 12 months and 24 months a 6 min walk test will be repeated (figure 1).

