**Figure 1 F1:**
[figure not shown]
Legend – participant flow through the study.

The majority of initial sample processing will be performed at the participant’s local NHS hospital trust via the Clinical Research Network. Participation in the study will be for 2 years. Other than initial assessment and follow-up visits at 3 months, 12 months and 24 months, there will be no further assessments. Only participants recruited at Nottingham University Hospitals NHS Trust will be offered a study bronchoscopy. It is not anticipated that any data will be obtained before completion of study that would lead to discontinuation of the study. For individual participants, discontinuation will be decided on an individual basis. The end of study will be defined as the last patient to complete the 2 years of follow-up.

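### Overall survival is assigned to a binomial model although the mortality end point has no fixed horizon; time-to-event modelling is kept for markers already identified

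*Protocol article*

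**What the plan says.** The Statistics section of the protocol article puts two outcomes under one model family: "Association of baseline biomarker levels with dichotomous disease progression and overall survival will be analysed using binomial family of generalised linear models". It attaches no link function, time offset, survival horizon or rule for participants who leave alive.

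The Objectives section lists the survival outcome as "All-cause mortality at time of censoring". The other seven secondary end points each carry a window (12 weeks, 12 months or 2 years); mortality does not. The primary end point has a fixed horizon: "Disease progression defined as relative forced vital capacity decline ≥10% or death within 12 months".

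Time-to-event modelling appears later in the Statistics section as a follow-on step: "Where putative biomarkers are identified, end point data will be used to compare biomarker levels by time-to-event through proportional hazard models". The end point is not named.

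On follow-up, the text after Figure 1 says "Participation in the study will be for 2 years" and "Other than initial assessment and follow-up visits at 3 months, 12 months and 24 months, there will be no further assessments", and defines the end of study by the last participant to finish two years. Selection of participants allows withdrawal at any time. Under Sample size justification, if the interim look does not show about 50% progression, later recruitment is enriched from the faster-progressing subgroups.

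**The concern.** Mortality counted up to a censoring time is time-to-event data. A binomial model of dead versus not dead, without a time term, gives the same code to a participant last seen alive at 3 months and one seen alive at 24 months. This suits a status known for everyone at one fixed time, such as 12-month progression. It does not suit an outcome with an open horizon and permitted withdrawal.

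The order of analysis adds to this. Finding markers that predict all-cause mortality is the first secondary objective. The model named for that association does not use time, while the model that does is reached only by markers already identified by some route. A marker that fails to get through has no planned time-to-event analysis of mortality, and any hazard ratios that follow are estimated on a selected set.

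At stake are false or masked mortality associations if length of follow-up is related to marker level. Loss of power is a lesser issue.

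**Working it through.** **No figure to reproduce.** The article gives no number of deaths, hazard ratio or power for overall survival. The check asks how much the choice of model could matter.

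**Step 1: what early censoring does.** Assume a constant hazard of 10% per year (not in the article).

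- The chance of dying by time t is 1 − exp(−0.10 t).
- A participant who withdraws alive at 3 months has 1.75 years left to month 24. The chance of death in that time is 1 − exp(−0.10 × 1.75) = 0.16. A binomial code of survivor at 24 months would be wrong with that probability.

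**Step 2: two readings of the censoring time.**

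- *24 months each.* Two years' participation and no later assessments fit this. Staggered entry then leaves planned follow-up equal, and only withdrawals differ.
- *One closing date, when the last participant finishes two years.* The interim look follows 100 participants who have completed one year. Anyone recruited after it entered at least 12 months later than those 100. The last entrant would have 24 months and those 100 at least 24 + 12 = 36.

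The outer bound under the second reading, at the same assumed hazard:

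| Follow-up | Died | Odds |
|---|---|---|
| 24 months | 0.181 | 0.221 |
| 36 months | 0.259 | 0.350 |
| 48 months (assumed) | 0.330 | 0.492 |

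Two groups with identical hazards would show an odds ratio of 0.221/0.350 = 0.63 (24 v 36 months) or 0.221/0.492 = 0.45 (24 v 48). These bounds require marker groups to coincide fully with follow-up groups.

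**Step 3: simulation of a less extreme case.** From the article: n = 200 and alpha 0.05 (taken as two-sided). Assumed: one standardised marker; exponential survival; two-year mortality of 15%, 30% or 45%; hazard ratio 1.5 per SD for power and 1.0 for type I error; where used, 20% dropout over two years unrelated to the marker, follow-up spread evenly over 2 to 4 years, and correlation 0.3 between marker and entry date. There were 500 replicates per scenario. Cells are logistic / Cox, in %.

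| Scenario | 15% mortality | 30% | 45% |
|---|---|---|---|
| Power, complete 24 months | 59.4 / 60.0 | 87.4 / 88.4 | 97.0 / 97.2 |
| Power, 24 months, 20% dropout | 54.2 / 56.0 | 84.0 / 86.6 | 93.8 / 94.6 |
| Power, 2-4 years | 76.8 / 78.8 | 95.2 / 94.8 | 98.2 / 99.0 |
| Type I error, complete 24 months | 5.4 / 5.6 | 6.0 / 6.2 | 5.6 / 5.4 |
| Type I error, 2-4 years, correlation 0.3 | 8.0 / 4.4 | 9.0 / 5.8 | 10.4 / 7.0 |

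The largest power loss is 86.6 − 84.0 = 2.6 points. In the last row the average odds ratio per SD is 0.92 to 0.93 although the true effect is nil; the average Cox hazard ratio is 0.99 to 1.00. In that scenario higher marker levels enter later, so a marker that truly raises mortality would tend to be masked.

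The Monte Carlo standard error near 5% is √(0.05 × 0.95/500) = 0.0097, about 1 point. The Cox value of 7.0% is about two standard errors above nominal, so these error rates are approximate.

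**The case against.** Several points can be made for the plan.

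- **Follow-up may be equal by design.** Two years each, with nothing after month 24, supports a common window at least as well as a closing date. This stands. A reader might infer that mortality associations are confounded with entry date as a matter of fact, or that an odds ratio of 0.45 is to be expected. The article supports neither. It states no accrual length and no follow-up of 36 or 48 months, enrichment is conditional on the interim result, and 0.45 compares groups defined wholly by length of follow-up.
- **A binomial family can take account of time.** A complementary log-log model over intervals is itself a binomial-family model. True, but the sentence attaches no interval or offset and treats survival together with a dichotomous end point.
- **Time-to-event analysis is planned.** It is, and putative markers may be identified through progression instead of through the mortality model. What remains is order and scope: no proportional hazards analysis of mortality is promised for all prespecified markers.
- **Proportional hazards applied to visit-based progression.** A reader might infer this and object that interval-censored FVC times would be treated as exact. The text refers to end point data without naming one, and mortality is a listed end point. The objection holds only if progression is meant.
- **A condensed article with an unseen analysis plan.** Silence on censoring details alone would be no finding. Here a model is named, and it does not suit the end point as the same article defines it.

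**Conclusion.** The concern holds in a limited form. The article names a binomial model for a mortality end point with no fixed horizon and permitted withdrawal, and reserves time-to-event modelling for markers already identified.

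- If mortality is fixed at 24 months for all, the harm is misclassified withdrawals and a power loss of about 3 points or less. With complete follow-up it nearly vanishes. The simulated dropout was unrelated to the marker, so withdrawal that depends on the marker is not covered by this figure.
- If one closing date is used and follow-up becomes linked to marker level, type I error is about 8-10% against 4-7% for Cox. This rests on an assumed 2 to 4 years of follow-up and an assumed correlation of 0.3.

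The article does not say which case applies. The primary analysis is untouched, because a binomial model suits 12-month progression. For a secondary end point this should be changed, and it does not threaten the study.

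**What to change.** 1. Analyse all-cause mortality by Cox regression for all ten markers named for the primary analysis under Specimen processing and analysis (MMP-7, CA-125, CA19-9, SP-D, CRPM, C3M, C6M, MUC5B, DSP, AKAP13). Start the clock at the baseline sample date and censor at the last date known alive.
2. State the censoring rule: either a 24-month horizon for everyone or a named closing date.
3. Keep the binomial model for 12-month progression.
4. Name the end point for the proportional hazards step. If it includes FVC progression, use a discrete-time (complementary log-log) or interval-censored model. Clinic FVC is measured only at baseline and at the later visits ("Further visits at 3 months, 12 months and 24 months will include further 40 mL blood sampling, QoL and full lung function analysis"), so onset is known only to within 0-3, 3-12 or 12-24 months, while death can be dated.

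The cost is a change of wording and minor extra analysis. Dates of death and last contact must be recorded. Classifying death within 12 months already needs some timing of death, but the article does not say that these dates are collected throughout follow-up.

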## Abstract

**Introduction:**

The Its Not JUST Idiopathic pulmonary fibrosis Study (INJUSTIS) is a multicentre, prospective, observational cohort study. The aims of this study are to identify genetic, serum and other biomarkers that may identify specific molecular mechanisms, reflecting disease endotypes that are shared among patients with progressive pulmonary fibrosis regardless of aetiology. Furthermore, it is anticipated that these biomarkers will help predict fibrotic activity that may identify patterns of disease behaviour with greater accuracy than current clinical phenotyping.

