### Sample size justification

A power calculation has been conducted using prior data obtained at 3 months in the PROFILE (Prospective Observation of Fibrosis in the Lung Clinical Endpoints) study of patients with IPF.^8^ The study demonstrated that 90 stable and 90 progressive individuals were sufficient to detect a twofold change in MMP7 with >90% power and 5% type I error rate. MMP7 was selected for power calculation as the most conservative of the biomarkers identified in the PROFILE Study, with the lowest threshold for biomarker change and least statistical precision, thus powering on MMP7 ensures that other biomarkers will be analysed with adequate power. The calculation demonstrates that a sample of 100 participants with progressive fibrosis and 100 with stable fibrosis will be large enough to detect dynamic differences in biomarkers over 3 months with 80% power and a type I error rate of 5% (α=0.05). Therefore 200 participants with ILD will be recruited assuming 50% disease progression. Fifty positive IPF controls will be recruited to take part in the study to benchmark progressive fibrotic lung disease but will not be included in the final analysis.

The study is also appropriately powered for genetic risk scores. An individual SNP with 25% minor allele frequency would have >70% power to detect an OR of 1.8 for stable versus progressive disease. The power for a risk score comprising multiple variants is expected to be greater. This assumes an additive genetic model, p<0.05, in 100 stable versus 100 progressive patients whereby with each additional marker added to the model the power is actually increased rather than reduced. The markers used will all be defined a priori based on data obtained from the PROFILE Study^7 8^ but are likely to include MUC5B, DSP, AKAP13, SP-D, CA-125, CA19-9, MMP-7, CRPM and C6M.

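### For markers, cut-offs and models chosen in this cohort, ROC accuracy is assessed in the same participants with no stated correction, so as written it is apparent accuracy and biased upward

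*Protocol article*

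**What the plan says.** The Statistics section sets an order of steps. Baseline biomarkers are first tested for association with progression by binomial generalised linear models. The end point "will be used dichotomously across all subgroups collectively analysed together, with the exception of IPF controls". Benjamini-Hochberg is applied where appropriate. The next step is conditional on that result: "Where putative biomarkers are identified, end point data will be used to compare biomarker levels by time-to-event through proportional hazard models", and in the same sentence "comparable ability to predict end points will be assessed through sensitivity and specificity analyses", by ROC curves.

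The same section plans "machine learning strategies on home spirometry to detect decline in lung function", followed by a comparison of sensitivity with traditional spirometry for predicting end points.

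Two kinds of marker feed these steps. Specimen processing and analysis names a primary panel of seven proteins and three genotypes. It also names an exploratory search by genome and RNA sequencing, proteomics and metabolomics for novel predictors. On the panel, Sample size justification says "The markers used will all be defined a priori based on data obtained from the PROFILE Study", although the list that follows is given only as likely.

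The cohort size is also fixed there: "Therefore 200 participants with ILD will be recruited assuming 50% disease progression". The 50 IPF controls "will not be included in the final analysis".

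**The concern.** Entry to the ROC step depends on a result obtained in the same participants and on the same outcome. A marker is more likely to pass when chance has pushed its observed AUC up, so the AUC reported after selection is too high on average. The same happens when a cut-off is picked from the ROC curve, or when a model is trained and scored on the same people.

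Nothing stated in the article offsets this. The cohort is pooled with no split described, and the IPF group is not available as a test set. Benjamini-Hochberg limits false discoveries but does not shrink the estimate for a marker that passes.

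Accuracy matters to the study's message, because the Abstract anticipates biomarkers that identify disease behaviour "with greater accuracy than current clinical phenotyping". In the home-spirometry comparison, a model tuned in the cohort would be set against a conventional measure that was not tuned there. Unless the model is scored on unseen data, that comparison favours the model.

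**Working it through.** **Stated figure.** The article gives no AUC, sensitivity or specificity. The figure that can be rebuilt at the same group sizes is the power for one SNP: more than 70% for minor allele frequency 25%, odds ratio 1.8, 100 versus 100, p<0.05 (two-sided assumed). With 200 alleles per group:
- 25% in stable patients: odds (0.25/0.75) × 1.8 = 0.60, frequency 0.60/1.60 = 0.375, power 77.1%.
- 25% in the pooled sample: frequencies 0.196 and 0.304, power 71.2%.

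Both agree with the article, so 100 versus 100 is used below.

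**Why selection inflates the AUC.** Under no association, the standard error of the AUC is √[(n₁+n₀+1)/(12·n₁·n₀)] = √(201/120,000) = 0.0409. If only one of k markers passes Benjamini-Hochberg at 5%, it needs p ≤ 0.05/k. The smallest apparent AUC that can pass is therefore 0.5 + z × 0.0409:
- k = 10: p ≤ 0.005, z = 2.81, AUC ≥ 0.615.
- k = 5,000: p ≤ 0.00001, z = 4.42, AUC ≥ 0.681.
- k = 20,000: p ≤ 0.0000025, z = 4.71, AUC ≥ 0.693.

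The floor falls when several markers pass together. A lone marker whose true AUC is 0.60 cannot be reported at 0.60 in any of these settings.

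**Simulation.** Independent normal markers, empirical AUC, Benjamini-Hochberg at 5%, 100 versus 100. The true AUCs and feature counts are assumptions. Values are averages over the markers that pass.

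| Setting | Apparent AUC | True AUC | Optimism |
|---|---|---|---|
| One a priori marker, always reported | 0.60 | 0.60 | 0.00 |
| 10 markers, all true 0.65 | 0.654 | 0.650 | 0.00 |
| 10 markers: three at 0.65, three at 0.60, four null | 0.643 | 0.627 | 0.02 |
| 10 markers, all true 0.60 | 0.624 | 0.600 | 0.02 |
| 10 markers: one at 0.60, nine null | 0.637 | 0.584 | 0.05 |
| 5,000 features, 20 at 0.65 | 0.687 | 0.645 | 0.04 |
| 20,000 features, 50 at 0.65 | 0.694 | 0.641 | 0.05 |
| 2,000 features, 20 at 0.60 | 0.679 | 0.586 | 0.09 |
| 5,000 features, 20 at 0.60 | 0.689 | 0.586 | 0.10 |

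The bias is largest when signals are weak and many features are searched. It shrinks as signals strengthen: with 50 features at a true AUC of 0.70 among 5,000 it is about 0.01.

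With 60 progressive and 140 stable, panel optimism is slightly larger: 0.633 against 0.600 for ten markers at 0.60, and 0.650 against 0.629 for the mixed panel.

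**Cut-offs.** One a priori marker with true AUC 0.60 has an unbiased AUC. With the cut-off chosen in the sample to maximise sensitivity plus specificity, however, apparent sensitivity and specificity are 0.61 and 0.59, against true values at that cut-off of 0.58 and 0.55.

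**Machine learning.** No size can be given, because the article states neither the number of home-spirometry participants nor the model. The direction is the same if models are scored on the data that trained them.

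**The case against.** The strongest objection is that this is silence, not a stated choice. A condensed article commonly leaves resampling to an analysis plan, and the list of approaches is expressly open. No sentence rules out internal validation. This stands as a limit on certainty and severity. It does not remove the point, because the article does commit to a sequence of selection, then ROC on the same end point data, in one pooled cohort.

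The second objection is that the primary panel was not picked here. That is correct: its candidates come from an external IPF cohort. A reader might infer that all reported accuracy will be too high, but the article does not support this. If every panel marker's AUC is reported, the selection bias is nil. Optimism enters the panel only through the in-study association screen, a data-chosen cut-off, or score weights fitted in this cohort.

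A reader might also infer very large bias from searches among pure noise. The best of 20,000 null features has an apparent AUC of about 0.67 against a true 0.50, and a logistic model on the top 10 of 5,000 null features reaches about 0.86. These figures ignore the multiplicity screen, and the second assumes a multi-marker model that the ROC sentence does not describe. With ten null markers, Benjamini-Hochberg passes something in only about 5% of studies, so usually no ROC step would follow.

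Finally, the omics and home-spirometry work is exploratory or secondary, the primary analysis is a test of association, and better accuracy is anticipated rather than claimed. All of this stands and limits the consequences.

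**Conclusion.** The point holds in a limited form. Followed as written, the article's sequence gives apparent accuracy, biased upward for markers, cut-offs or models chosen in this cohort. At 100 versus 100 with the Benjamini-Hochberg screen, AUC optimism is about 0.01 to 0.05 for panel markers carrying signal and about 0.04 to 0.10 for markers found among 5,000 to 20,000 features. These sizes rest on assumed feature counts, true AUCs of 0.60 to 0.65 and independent markers; stronger markers would show less. The primary association test is not affected. Severity is minor to moderate, and lower still if an analysis plan already specifies validation.

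**What to change.** Add to the Statistics section, or confirm in the analysis plan, wording such as:

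> For any marker, cut-off or multi-marker model selected in this cohort, and for the machine-learning models on home spirometry, selection, cut-off choice and fitting will be repeated inside bootstrap resampling or nested cross-validation. The optimism-corrected AUC, sensitivity and specificity will be reported with their intervals. The AUC of every a priori panel marker will be reported regardless of significance. Any uncorrected ROC result will be labelled apparent.

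The selection step must be inside the resampling loop; resampling only the final model leaves the selection bias in place. The cost is computing time and somewhat lower reported accuracy. No new data are needed.

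### The only methods tied to the two-year exacerbation count, correlation and ANOVA, ignore time at risk, so associations for markers that also raise mortality would be attenuated and lose power

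*Protocol article*

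**What the plan says.** All references are to the protocol article.

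- **Objectives.** Finding biomarkers that predict complications, acute exacerbations among them, is a secondary objective. The matching secondary end point is "Number of acute exacerbations over 2 years", a count with no person-time denominator. All-cause mortality is a separate secondary end point.
- **Study regimen (text after Figure 1).** "Participation in the study will be for 2 years", so the count is complete only for participants who survive and stay in the study.
- **Statistics, exploratory secondary objectives.** Markers already identified are carried forward. The list opens with "Statistical approaches include, but are not limited to" and the item on exacerbations is "correlation and analyses of variance between biomarker levels and patient-reported QoL outcomes or disease exacerbations". After a reference to factor analysis, the paragraph closes with "generalised linear models will be used to test associations".
- **Statistics, first paragraph.** "Gaussian family or otherwise appropriate models will be used to assess associations with continuous secondary end points" covers continuous end points and does not mention counts. For putative biomarkers, "end point data will be used to compare biomarker levels by time-to-event through proportional hazard models", with no link to exacerbations and no stated treatment of death as a competing event.

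**The concern.** A participant who dies at eight months cannot have an exacerbation in the remaining sixteen. Correlation and ANOVA on the raw count treat that participant as if observed for the full two years. This would be harmless if early death were unrelated to the marker. Here it may well be related: the primary end point includes death, prediction of mortality is a secondary objective, and markers identified in those analyses are the ones passed on to the exacerbation analysis. Where a marker raises both the exacerbation rate and the risk of death, shortened follow-up offsets part of the excess exacerbations. At stake is a stated secondary objective: a real association could be underestimated or missed.

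**Working it through.** The article gives no rate, power or sample size for exacerbations, so there is no planned figure to reproduce.

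**Inputs from the article.** Follow-up is 2 years. The analysed sample is 200, with IPF controls excluded (Sample size justification). The only survival figure is the median of 3 years for IPF (Introduction). If survival is exponential, two-year mortality is 1 - 0.5^(2/3) = 0.37. The four analysed groups have no mortality figure, so 37% serves only as the top of an assumed range of 10-37%.

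**Assumed inputs.** Exacerbation rate, marker rate ratio (RR) and marker hazard ratio (HR) for death are not in the article.

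**Step 1: size of the bias, two equal groups (100 high, 100 low marker).** With a constant death hazard λ, expected time at risk within two years is

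E[T] = (1 - exp(-2λ)) / λ

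With a constant exacerbation rate, the raw-count ratio is

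crude ratio = RR × E[T, high] / E[T, low]

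Example: 37% dead overall and HR 3 give λ = 0.123 (low) and 0.369 (high).
- Low: (1 - exp(-0.246)) / 0.123 = 1.77 years
- High: (1 - exp(-0.738)) / 0.369 = 1.41 years
- Ratio of follow-up: 0.80, so a true RR of 1.5 appears as 1.5 × 0.80 = 1.20

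| Dead at 2 years | Follow-up ratio, HR 2 to HR 4 | True RR 1.5 appears as | True RR that would be cancelled |
|---|---|---|---|
| 10% | 0.97 to 0.94 | 1.45 to 1.41 | 1.04 to 1.07 |
| 20% | 0.93 to 0.87 | 1.40 to 1.31 | 1.08 to 1.14 |
| 37% | 0.86 to 0.76 | 1.30 to 1.14 | 1.16 to 1.32 |

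The last column is the inverse of the follow-up ratio.

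**Step 2: power, two groups.** 1000 simulated data sets per scenario; 0.2 exacerbations per year, RR 1.5, HR 3:

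| Dead at 2 years | ANOVA on raw counts | Rate analysis |
|---|---|---|
| 10% | 42% | 52% |
| 20% | 25% | 45% |
| 37% | 12% | 43% |

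Across all scenarios run, the rate analysis recovered the true ratio (mean estimates 0.97-1.01 for RR 1, 1.49-1.54 for RR 1.5, 1.98-2.05 for RR 2).

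**Step 3: continuous marker.** n = 200, 0.3 exacerbations per year, death HR 1.5-2.0 per SD, true RR 1.3 per SD:

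| Two-year mortality | Raw-count RR per SD | Power, correlation | Power, rate model with offset |
|---|---|---|---|
| 10% | 1.23-1.27 | 38-52% | 60-68% |
| 30% | 1.12-1.20 | 12-34% | 55-57% |

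These values are approximate. They move with the assumed between-patient variation and with how mortality is set. The comparison changes both the model family and the offset, so not all of the power gap is due to shortened follow-up.

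**Step 4: a marker with no effect on the exacerbation rate.** In the two-group simulation with HR 2-3, ANOVA called such a marker significantly protective in 3-23% of data sets, against a nominal 2.5% in that direction. The figure exceeded 10% only at 37% mortality with at least 0.2 exacerbations per year.

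**The case against.** The strongest reply is that the list is open and already includes generalised linear models, the family to which a Poisson or negative binomial model belongs; the choice of family and offset is ordinary analysis-plan detail. This stands in part. A reader might infer that the protocol commits to correlation and ANOVA alone, and the article does not support that: it permits a correct analysis. But the two methods it does attach to exacerbations are the ones that ignore time at risk, and a generalised linear model on raw counts without an offset has the same bias. The proportional hazards sentence is not tied to exacerbations and does not analyse a count.

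A reader might also infer that the markers were selected because they predict death. The article does not say so; Sample size justification says they are defined a priori from an earlier IPF cohort and frames them as separating stable from progressive disease. The concern is therefore conditional on a marker-death association.

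The bias is small if few participants die. At 10% mortality, 0.2 exacerbations per year and HR 1.5-2.0 per SD, a true RR of 1.3 appears as 1.27-1.25, power is 42-47% v 57%, and correlation rejects a true null in 5-6% of runs, no more often than the rate model (6-8%).

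Finally, the main simulations take death as independent of exacerbations given the marker. Two ways of relaxing this moved the result in opposite directions:
- With 30% of exacerbations fatal (30% mortality, HR 2), the power of correlation rose from 13% to 24%, against 52% for the rate model.
- With exacerbations tripling the death hazard (30% baseline mortality, HR 1.75), it fell from 17% to 13%, against 49%.

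A power loss remained in both.

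**Conclusion.** The point holds as a conditional one. For a marker that also raises mortality, the named methods understate its association with exacerbations and lose power, modestly at 10% two-year mortality and substantially at 30% or more. A reader might go further and expect such markers to look protective or lose their association altogether. The figures do not support that as the usual result: a true RR of 1.3 or 1.5 stays above 1 in every setting tabulated above, and cancellation or reversal needs a null or weak true effect together with substantial mortality and a strong marker-death link.

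The size rests on assumed exacerbation rates, effect sizes and non-IPF mortality, none of which the article gives. Priority is low to moderate. The analysis is described as exploratory, mortality is analysed separately, and the primary end point counts death as an event, so no primary conclusion is affected.

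**What to change.** In the Statistics section, where exploratory secondary objectives are described, specify that the generalised linear model for exacerbations is a negative binomial (or Poisson with robust standard errors) regression with log follow-up time as offset and the covariates already planned. Add time to first exacerbation with death as a competing event as a supporting analysis. Keep correlation and ANOVA for description only.

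The cost is a change of wording and slightly more analysis work. No new data should be needed, since the mortality end point and the proportional hazards models already require follow-up times. One limit should be stated with the result: the rate describes exacerbations while participants are alive, so it should be read beside the mortality analysis.
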